**Research protocol: part 1**

**Project summary**

This study investigates the therapeutic potential of ultrasound-guided fascia hydrorelease (US-FHR) around cervical arteries for patients with cervical myofascial pain syndrome (MPS). Adults aged 20 years or older with cervical pain diagnosed as MPS and reporting movement-evoked pain of at least 30 mm on the visual analog scale (VAS) will be enrolled. The intervention targets the transverse cervical or dorsal scapular artery, which supply the trapezius, levator scapulae, and related cervical soft tissues. Under real-time ultrasound guidance, saline will be injected into the periarterial fascial planes to release adhesions and potentially improve local blood flow and tissue mobility.

The primary objective is to determine whether periarterial US-FHR produces clinically meaningful reductions in cervical pain intensity, assessed by VAS at rest and during neck movement at baseline and follow-up. Secondary objectives include evaluating changes in arterial blood flow using Doppler ultrasound and assessing improvements in activities of daily living (ADL) with validated disability questionnaires. Safety will be monitored by recording adverse events related to the injection procedure, including bleeding, hematoma, and infection. By integrating subjective pain outcomes, objective hemodynamic measurements, and functional indices, this study aims to clarify whether ultrasound-guided periarterial fascia hydrorelease can serve as a safe and effective treatment option for patients with cervical MPS and significant movement-evoked pain.

**Rationale & background information**

Shoulder stiffness is a highly prevalent condition, ranking first among women (113.3 per 1,000 individuals) and second among men (57.2 per 1,000 individuals), according to the 2019 Comprehensive Survey of Living Conditions conducted by the Ministry of Health, Labour and Welfare of Japan. Although ischemia of the shoulder girdle and cervical tissues has been suggested as a possible cause of shoulder stiffness and neck pain, few treatment strategies have directly aimed to improve blood flow.

In diseases associated with chronic pain around the shoulder joint, development of abnormal neovascularization has been reported, and embolization of these vessels to normalize local blood flow has led to pain reduction (Okuno Y, et al. J Vasc Interv Radiol. 2022 Dec;33(12):1468–1475). These findings suggest that normalization of local tissue perfusion could serve as a causal treatment for chronic pain.

Furthermore, fascia has recently attracted attention as a therapeutic target for pain. Fascia is a three-dimensional fibrous network that envelops muscles, vessels, and nerves throughout the body, connecting organs and mediating mechanical and informational interactions. It serves to facilitate smooth organ movement, provide structural support, protection, and maintain positional stability. Pathological changes in fascia—such as adhesion or decreased gliding and elasticity—can contribute to pain. Using ultrasound imaging, fascia hydrorelease (US-FHR) is a procedure in which fluid is injected to mechanically separate and relax thickened, hyperechoic fascia by moving the needle tip within it. This technique aims to improve not only pain symptoms but also fascial flexibility, glide, and extensibility (modified from the Japan Society of Ultrasonics in Medicine website: https://www.jnos.or.jp/for_medical).

Our co-investigator, [name], has reported that ultrasound-guided fascia hydrorelease targeting the coracohumeral ligament in patients with painful shoulder stiffness improved both shoulder range of motion and pain ([name] H, Suda M, et al. Sci Rep. 2022 Nov 17;12(1):19782). Subsequently, we observed that performing fascia hydrorelease on arteries supplying the painful region—particularly those exhibiting fascial thickening, kinking, branching, or stenosis—resulted in improved arterial blood flow and alleviation of pain symptoms. However, these findings have not yet been scientifically evaluated.

**Study goals and objectives**

In this study, we performed ultrasound-guided fascia hydrorelease around the transverse carotid artery that feeds the trapezius and levator scapulae muscles and other neck tissues in patients diagnosed with stiff neck pain and myofascial pain syndrome (MPS) in the neck. We want to clarify whether or not pain symptoms can be improved by ultrasound-guided fascia hydrorelease around the transverse cervical artery or the dorsal scapular artery that feeds the trapezius, levator scapulae, and other neck tissues.

The primary outcome was neck pain, measured using the VAS scale during neck movement, assessed 15 min after US-FHR and compared with the baseline value.

The secondary outcomes were: (1) neck pain VAS score during neck movement, assessed 1 week after US-FHR; (2) pain VAS score at rest, assessed 15 min and 1 week after the procedure; (3) blood flow volume at the FHR-treated site, measured by ultrasound immediately and 1 week after US-FHR; (4) ADL, assessed using the PDI-5-J before and 1 week after US-FHR; and (5) Surface temperature, measured by thermographic camera before, immediately after, and one week after US-FHR.

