**Study design**

We conducted a prospective, single-arm interventional study to assess the effectiveness of US-FHR in adult patients (aged >20 years) who presented with neck pain to the outpatient departments of [name] Pain Clinic or Isesaki Municipal Hospital between May 1, 2024, and February 28, 2025.

The inclusion criteria were as follows: patients clinically diagnosed with MPS corresponding to chronic primary musculoskeletal pain (MG30.02 according to the International Classification of Diseases, 11th Revision criteria) for nonspecific chronic neck pain, a movement-related pain VAS score of ≥30 mm, and willingness to undergo FHR treatment. Patients were excluded if they: had been diagnosed with conditions that may cause secondary chronic neck pain, such as a history of head or neck trauma, neurological disorders, inflammatory diseases, or tumors; received an additional prescription for analgesics from 1 week before to 1 week after the FHR procedure; could not safely discontinue anticoagulant or antithrombotic therapy, had a bleeding tendency, or showed signs of infection at the planned FHR site; had difficulty in evaluating blood flow in the transverse cervical or dorsal scapular artery using ultrasound; and planned to undergo FHR at other anatomical sites during the study period.

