**Expected outcomes of the study**

If this study scientifically demonstrates that pain can be treated by US-FHR around blood vessels, it will provide a new therapeutic option for pain management.

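### The only primary time point is 15 minutes after the injection, yet the closing claim for a chronic pain population carries no duration, and the Project summary words the primary objective differently

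*Protocol*

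**What the plan says.** Protocol, Study goals and objectives, repeated under Outcome measurements in Methodology: the single primary endpoint is pain in the neck, "measured using the VAS scale during neck movement, assessed 15 min after US-FHR and compared with the baseline value". The first secondary outcome is "1) neck pain VAS score during neck movement, assessed 1 week after US-FHR". Resting VAS, blood flow, surface temperature and PDI-5-J are also read at 1 week; PDI-5-J has no other reading after treatment.

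Protocol, Study design: a single-arm study in "patients clinically diagnosed with MPS corresponding to chronic primary musculoskeletal pain".

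Protocol, Follow-up: patients are observed for about 20 minutes after the procedure, so the primary reading falls inside that period.

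Protocol, Project summary: the primary objective concerns pain intensity "assessed by VAS at rest and during neck movement at baseline and follow-up". The same section ends with the aim of clarifying whether the procedure "can serve as a safe and effective treatment option for patients with cervical MPS and significant movement-evoked pain", to be judged from pain, blood flow and functional measures taken together.

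Protocol, Expected outcomes of the study: if treatability of pain is demonstrated, "it will provide a new therapeutic option for pain management".

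Protocol, Data management and statistical analysis: the sample size rests on a one-sample t-test of a 20 mm mean change with SD 35 mm, without saying at which time. The analysis uses Wilcoxon signed-rank tests at both times with a Bonferroni correction, whose family is not stated.

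**The concern.** Shortly after a needle and 2 mL of saline, an acute response to the injection cannot be told apart from relief that lasts. For a chronic condition, duration is part of what makes something a treatment option. The only reading of the primary pain measure that bears on persistence is the 1-week movement VAS, which is secondary. The Expected outcomes section does not refer to it, and the Project summary brings in data that exist only at 1 week solely through the functional index.

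The primary objective also appears in two forms. The Project summary includes pain at rest and leaves the time open; Study goals and Methodology restrict it to movement pain at 15 minutes. The sections on safety and follow-up use the term follow-up visit for the 1-week visit, so a reader of the summary could take the primary time to be 1 week. What is at stake is a claim wider than the primary result can carry, and doubt about which result is primary.

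**Working it through.** **Inputs.** From the protocol's sample size section: mean change 20 mm, SD 35 mm, two-sided alpha 0.05, power 0.80, 28 evaluable, about 20% dropout, 35 enrolled. Assumptions of this review: SD 35 mm at both times, 1-week effects of 0 to 20 mm, and correlation between the two changes of 0 to 0.8. The t-test is used because it is the protocol's planning test; the planned analysis is Wilcoxon.

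**1. The plan's own figure.** d = 20/35 = 0.571. The noncentral t calculation gives n = 27 (power 0.815); n = 28 gives 0.830. Dropout: 28/(1 − 0.20) = 35. The stated 28 and 35 are sound, so this is not an arithmetic error.

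**2. Smallest significant mean change at 15 minutes**, t × SD/√n:

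| Evaluable | Alpha 0.05 | Alpha 0.025 (Bonferroni, if the family is the two times) |
|---|---|---|
| 28 | 2.052 × 35/√28 = 13.6 mm | 2.373 × 35/√28 = 15.7 mm |
| 35 | 2.032 × 35/√35 = 12.0 mm | 2.345 × 35/√35 = 13.9 mm |

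The row for 35 applies if nobody is lost before the 15-minute reading, which is taken at the treatment visit. The protocol does not define the Bonferroni family, so 12.0 to 15.7 mm is a range over these assumptions.

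**3. Relief at 15 minutes only** (true change 20 mm at 15 minutes, 0 mm at 1 week). The primary t-test at 0.05 is significant with probability 0.83 (n = 28) or 0.91 (n = 35). Requiring a significant 1-week benefit as well brings this to about 0.020 to 0.026 at n = 28 (simulation, correlation 0 to 0.8). The primary test alone does not distinguish transient from lasting relief; the pair of tests does.

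**4. Alpha for the 15-minute test.** Power at n = 28 for 20 mm is 0.83 at 0.05, against 0.74 at 0.025. A fixed sequence that starts with 15 minutes keeps the full 0.05 there.

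**5. Power at 1 week with 28 evaluable.**

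| True 1-week change | Power, 1-week test alone | Evaluable needed for 80% |
|---|---|---|
| 20 mm | 0.83 | 27 |
| 15 mm | 0.59 | 45 |
| 10 mm | 0.31 | 99 |

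Both tests positive, with 20 mm at each time: 0.69 (correlation 0) to 0.77 (correlation 0.8). To reach 80% for both would take about 34 down to 30 evaluable, or 43 down to 38 enrolled.

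**The case against.** A reader might infer that the trial would be declared a success, and the treatment-option conclusion reached, even with pain back at baseline after 1 week. The document does not go that far. It never calls any test confirmatory and states no rule for success. The Expected outcomes sentence is conditional and is not tied to the 15-minute P-value. The Project summary rests its conclusion on several kinds of outcome together, and one of them, PDI-5-J, can only be a 1-week result. The objective in Study goals asks whether pain can be improved and promises no duration. Movement VAS at 1 week is the first secondary outcome and is tested against baseline, so a lost effect would be seen. An immediate endpoint is defensible for a procedure that the protocol says has not yet been scientifically evaluated, and the order of secondary tests is commonly left to a statistical analysis plan.

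All of this stands, and it removes the stronger reading. It does not remove two things fixed in the protocol's own text: an unqualified claim beside a 15-minute primary outcome, and two wordings of the primary objective.

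It is also fair to object that a 1-week result would not settle efficacy. In a single-arm study with analgesics permitted, change at 1 week cannot be separated from natural course or other influences. The claim must therefore stay limited even when both tests are positive.

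**Conclusion.** The point holds as a mismatch between the primary time point and the breadth of the stated claim, together with an internal inconsistency in the primary objective. The choice of 15 minutes is not itself an error. On the planning SD, the primary result alone would be positive about 83% of the time (28 evaluable, alpha 0.05) for a 20 mm effect that had gone by 1 week. That figure is a t-test approximation to the planned Wilcoxon test and is 0.74 if Bonferroni over two times applies. The 1-week effect sizes and correlations are assumptions, since the protocol gives one 20/35 mm figure without a time. A change is worthwhile because it is cheap and uses data already planned.

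**What to change.** 1. **Project summary:** reconcile the primary objective with Study goals and Methodology, naming one measure (rest or movement) and one time.
2. **Statistical analysis:** test movement VAS at 15 minutes at two-sided 0.05 and, only if that is positive, movement VAS at 1 week at two-sided 0.05. State that this fixed sequence replaces Bonferroni for these two tests.
3. **Project summary and Expected outcomes:** say that a positive 15-minute result alone supports only an immediate pain reduction after the procedure. Any treatment-option wording should also need a positive 1-week result, be limited to up to 1 week, and be described as an uncontrolled before-after change.
4. **Timing:** parts of the protocol are in the past tense, and recruitment ends in February 2025 in Study design but March 2026 in Duration of the project. If data have already been examined, label the change as made afterwards.

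**Cost:** wording only, with no new visits, measurements or patients, and no alpha lost for the 15-minute test. The downside is a narrower claim if 1 week is not positive, which is a real risk given the power figures above. A sponsor who wants 80% power for both tests would need a larger sample, on the assumptions shown.

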**Study design**

We conducted a prospective, single-arm interventional study to assess the effectiveness of US-FHR in adult patients (aged >20 years) who presented with neck pain to the outpatient departments of [name] Pain Clinic or Isesaki Municipal Hospital between May 1, 2024, and February 28, 2025.

The inclusion criteria were as follows: patients clinically diagnosed with MPS corresponding to chronic primary musculoskeletal pain (MG30.02 according to the International Classification of Diseases, 11th Revision criteria) for nonspecific chronic neck pain, a movement-related pain VAS score of ≥30 mm, and willingness to undergo FHR treatment. Patients were excluded if they: had been diagnosed with conditions that may cause secondary chronic neck pain, such as a history of head or neck trauma, neurological disorders, inflammatory diseases, or tumors; received an additional prescription for analgesics from 1 week before to 1 week after the FHR procedure; could not safely discontinue anticoagulant or antithrombotic therapy, had a bleeding tendency, or showed signs of infection at the planned FHR site; had difficulty in evaluating blood flow in the transverse cervical or dorsal scapular artery using ultrasound; and planned to undergo FHR at other anatomical sites during the study period.

**Methodology**

Intervention

Patients underwent US-FHR around the target artery during their first visit. Figure 4 illustrates the US-FHR procedure. Patients were positioned in the lateral decubitus position with the treatment site facing upward and the arm placed alongside the torso. US-FHR was performed using a Canon Aplio i700 ultrasound system (authentication number: 228ABBZX00022000) with an i18LX5 probe (frequency range: 4–18.3 MHz; authentication number: 228ABBZX00025000). The probe was placed medial to the acromion to visualize the trapezius and supraspinatus muscles, enabling identification of the artery located between them. The arteries supplying the cervical tissues exhibit considerable anatomical variation; at this site, either the transverse cervical or dorsal scapular artery can be visualized. The artery closest to the pain source and most easily visualized was selected as the target for intervention. After identifying the transverse cervical or dorsal scapular artery that supplies the cervical tissues, arterial blood flow was assessed. US-FHR was then performed at the stacked fascia surrounding the artery. A 27-gauge, 38-mm needle and a 10-mL syringe were used for the injection. Using the out-of-plane technique, the needle tip was visualized around the artery, and 2 mL of normal saline was injected into the stacked fascia around the artery. The artery diameter and blood flow were reassessed at the same location 2 min after performing US-FHR. A video recording of each procedure was made. Patients who were taking analgesics on a regular schedule were instructed to continue their usual medication regimen without interruption or dose modification.

Outcome measurements

The primary outcome was neck pain, measured using the VAS scale during neck movement, assessed 15 min after US-FHR and compared with the baseline value.

The secondary outcomes were: (1) neck pain VAS score during neck movement, assessed 1 week after US-FHR; (2) pain VAS score at rest, assessed 15 min and 1 week after the procedure; (3) blood flow volume at the FHR-treated site, measured by ultrasound immediately and 1 week after US-FHR; (4) ADL, assessed using the PDI-5-J before and 1 week after US-FHR; and (5) Surface temperature, measured by thermographic camera before, immediately after, and one week after US-FHR. All secondary outcomes were compared with baseline values. Pain VAS scores were determined by measuring the distance (mm) from the “no pain” anchor and the patient’s mark on a 100-mm line, providing a score range of 0–100. Pain at rest and during movement were scored separately. Blood flow in the transverse cervical or dorsal scapular artery was evaluated immediately before and 2 min after US-FHR during the first and second visits. Arterial blood flow at the planned US-FHR site was measured as follows. First, an image of the vessel along its long axis was obtained, and the maximum diameter was recorded. After confirming arterial blood flow using the Superb Microvascular Imaging (SMI) mode, measurements were performed in Pulsed Wave mode. To ensure reliability, the sampling gate was set to two-thirds of the vessel diameter, and the angle correction was maintained below 60°. The blood flow waveform was observed, and the start and end points of one cardiac cycle were visually determined to trace a single heartbeat. Vessel diameters at the measurement site were recorded. To accurately capture the vessel lumen, the SMI flow display was removed, and the image was magnified to enhance clarity. The vessel diameter was measured as the distance between the inner walls of the lumen, and the cross-sectional area was calculated assuming a circular shape. The ultrasound system software then automatically calculated and displayed the corresponding blood flow volumes, which were recorded. At the second visit, blood flow was measured at the same site as during the first visit by reproducing identical imaging conditions. To ensure consistency, images from the previous measurement were printed, and confirmation was made that the trapezius and supraspinatus muscles, and either the transverse cervical or dorsal scapular artery, were visualized in the same manner before proceeding with the measurement. The PDI-5-J, assessed from the first visit (surveyed before US-FHR) to the second visit, was also included as a secondary outcome measure. The PDI-5-J (five-item Japanese version of the Pain Disability Index) is a self-report questionnaire designed to evaluate the degree to which pain interferes with five domains of daily activities: Family/Home Responsibilities, Recreation, Social Activity, Occupation, and Self-Care. Respondents rate their level of disability in each domain on an 11-point scale ranging from 0 (no disability) to 10 (total disability). The total score ranges 0–50, with higher scores indicating a greater degree of pain-related disability. The PDI-5-J was developed by omitting the items on sexual behavior and life-support activities from the original seven-item PDI, reflecting cultural considerations and respondent comfort in Japan. The PDI-5-J has demonstrated good reliability and validity for evaluating pain-related interference with daily activities among Japanese individuals with chronic pain. The painful site was identified, and its surface temperature was measured using a thermographic camera (FLIR C5™, FLIR® Systems, Inc.) before, immediately after, and one week after US-FHR. The use of analgesics was permitted during the study period; however, FHR, trigger point injections using local anesthetics or steroids, and acupuncture therapy were not allowed during the time between the first and second visits.

[figure not shown]

Figure 1. Flowchart of patient selection and treatment.

Abbreviations: PDI-5-J, five-item Japanese version of the Pain Disability Index; US-FHR, ultrasound-guided fascia hydrorelease; VAS, visual analog scale.

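### Blood flow rests on one hand-bounded heartbeat and a squared diameter with no averaging described, which adds avoidable random noise to a secondary, mechanistic outcome

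*Protocol*

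**What the plan says.** The protocol's Methodology section (Outcome measurements) sets out the flow measurement step by step.

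- **Velocity.** After the pulsed-wave recording, "the start and end points of one cardiac cycle were visually determined to trace a single heartbeat".
- **Diameter.** At the start, "an image of the vessel along its long axis was obtained, and the maximum diameter was recorded"; whether this value enters the flow calculation is not said. Later, "Vessel diameters at the measurement site were recorded", with no count of readings.
- **Area.** "The vessel diameter was measured as the distance between the inner walls of the lumen, and the cross-sectional area was calculated assuming a circular shape".
- **Flow.** "The ultrasound system software then automatically calculated and displayed the corresponding blood flow volumes, which were recorded".

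The safeguards stated are that "the sampling gate was set to two-thirds of the vessel diameter, and the angle correction was maintained below 60" degrees, that the image was magnified with the flow overlay switched off, and, for the second visit, "To ensure consistency, images from the previous measurement were printed". No repeat tracing, averaging or repeatability check is described.

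Flow is secondary outcome (3). The Rationale section presents better arterial flow as accompanying pain relief, so this outcome carries the mechanistic argument. The sample size is set on VAS change alone.

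**The concern.** Flow is mean velocity multiplied by cross-sectional area. One beat carries the full beat-to-beat variation, plus the error of placing its limits by eye. Area depends on the square of the diameter, so caliper error is amplified. Both errors enter the before-after difference twice, once at each time point.

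The stated safeguards deal with beam geometry, lumen visibility and finding the same site again. None of them averages out beat or caliper error. An analysis plan cannot repair this later, because the acquisition rule is fixed in the protocol and readings never taken cannot be averaged.

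At stake is the precision of the flow result in about 28 evaluable participants. A real change in flow could be missed, or estimated with an interval too wide to support or refute the proposed mechanism.

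**Working it through.** **Inputs from the protocol.** One cycle per measurement, circular area and an unstated number of diameter readings (Methodology). Wilcoxon signed-rank test against baseline, Bonferroni correction and 28 evaluable participants (Data management and statistical analysis).

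**Assumed, because the protocol gives no figure.** Single-beat velocity CV of 5/10/15% and single-reading diameter CV of 3/5/10%, paired as low/mid/high; independent errors; one diameter reading per flow value.

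**Step 1: the plan's own figure.** The only precision figure is the VAS sample size. With d = 20/35 = 0.571 and two-sided alpha 0.05, the exact one-sample t-test has power 0.7996 at n = 26, 0.815 at n = 27 and 0.830 at n = 28. The stated 28 is therefore adequate, and 28/(1 - 0.20) = 35. Both figures concern VAS and are unaffected. There is no counterpart for flow.

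**Step 2: squaring.** Flow = velocity × π d²/4. A diameter error of +3/+5/+10% gives a flow error of 1.03² - 1 = +6.1%, 1.05² - 1 = +10.3% and 1.10² - 1 = +21.0%.

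**Step 3: noise in one reading and in the change.** CV(flow) = √(CV_beat² + 4·CV_diam²). The mean of three independent complete readings divides this by √3. The before-after difference multiplies it by √2.

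| Case | CV, one reading | CV, mean of three | SD of change, one | SD of change, three |
|---|---|---|---|---|
| Low | √(0.0025 + 0.0036) = 7.8% | 4.5% | 11.0% | 6.4% |
| Mid | √(0.0100 + 0.0100) = 14.1% | 8.2% | 20.0% | 11.5% |
| High | √(0.0225 + 0.0400) = 25.0% | 14.4% | 35.4% | 20.4% |

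The reduction is 1 - 1/√3 = 42% in every row. It follows from averaging three independent readings and says nothing specific about this trial.

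**Step 4: why 42% is a ceiling.**

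- *Shared error.* Beats on one strip share gate position and angle correction, and calipers on one image share that image. If the three readings' errors correlate at ρ, the reduction is 1 - √((1 + 2ρ)/3): 42% at ρ = 0, 29% at ρ = 0.25 and 18% at ρ = 0.5 (ρ is assumed).
- *Diameters perhaps already repeated.* If three diameters were in fact averaged, the present CV is √(CV_beat² + 4·CV_diam²/3) = 6.1/11.5/18.9%. Moving to three beats then gives 4.5/8.2/14.4%, a gain of 26/29/24%.

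**Step 5: total SD of change.** Participants also differ in their true change. If the SD of the true log change is assumed to be 0.3, the total SD is √(0.3² + measurement variance). It goes from 0.320 to 0.307 (low), 0.361 to 0.321 (mid) and 0.464 to 0.363 (high), which are falls of about 4, 11 and 22%.

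**Step 6: illustrative power.** The setting is n = 28, a true rise in flow of 20%, and a t-test on log flow standing in for the signed-rank test. Alpha is 0.025, assuming Bonferroni over two follow-up times, because the number of comparisons is not stated. Readings are independent, as in Step 3.

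| SD of true log change (assumed) | One reading: low/mid/high | Mean of three: low/mid/high |
|---|---|---|
| 0.2 | 96/84/51% | 98/96/84% |
| 0.3 | 74/62/40% | 78/73/62% |
| 0.4 | 49/43/30% | 51/49/42% |

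The gain runs from about 2 to 33 points and is only 2 to 4 points in the low-noise cases.

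**The case against.** Several points on the other side are sound.

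- **The size is assumed.** Every CV is assumed. If noise is low, averaging buys little power. This stands and limits how strongly the point can be put.
- **The outcome is secondary.** No conclusion about pain depends on it. This stands too.
- **Controls already exist.** They do, and patients whose flow is hard to evaluate are excluded. These measures address other sources of error.
- **Feasibility.** Much of the protocol is in the past tense, and a reading is fixed at 2 minutes after the procedure. Consecutive beats on one strip take only seconds, however, and calipers can be repeated on the frozen image afterwards. The Study design section ends the patient window in February 2025, while Duration of the project runs recruitment to 31 March 2026, so the number of participants still to be measured is unclear. The protocol mentions procedure videos and printed images but does not say that spectral strips were stored.

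A reader might also infer more than the text supports:

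- *That the protocol presents single-beat tracing as ensuring reliability.* That wording is attached only to the gate width and angle correction.
- *That only one diameter was read.* The count is not stated, and the plural is used once. The squared diameter term is half or more of the flow variance in each case above, so this matters to the size.
- *That the operator picked favourable beats.* The protocol does not say who traced the beat or how it was chosen. Masking of the reader is a separate question, and averaging beats on a strip chosen by the same operator would not settle it.

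**Conclusion.** The point holds as a modest one about precision. The protocol fixes velocity at one beat bounded by eye, squares a diameter whose number of readings is not stated, and describes no averaging. Under the assumed CVs, one flow reading carries an error of about 8-25%. Averaging three would remove at most 42% of the independent within-session part, and less where readings share a strip, angle or image. With the SD of true log change assumed to be 0.3, the total SD of change would fall by about 4-22% even with fully independent readings.

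The 42% should not be read as the gain to expect in this trial. Random noise of this kind does not by itself bias the before-after comparison, and the primary VAS outcome and its sample size are unaffected. This is a cheap improvement; it does not invalidate the study.

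**What to change.** State in the Methodology section that, at every time point, at least three consecutive cardiac cycles are traced on the same frozen strip, three inner-wall diameter readings are taken at the sampling site, and the mean flow is analysed. Both parts are needed: averaging beats alone leaves the squared diameter term as it is. State also how many diameter readings have been taken so far and whether the maximum diameter enters the flow calculation.

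For participants already measured, re-trace all time points where strips were stored. Where they were not, do not mix one-beat and three-beat values within a participant, and report the single-beat method as a limitation of the flow result. The three readings also allow within-session repeatability to be reported.

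The cost is a few more minutes of reading per measurement, with the same operator and machine and no added procedure.
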